**Inclusion criteria**
Patients treated at the Emergency Department of Riotinto Hospital during the study and follow-up periodPatients presenting with acute de novo abdominal pain, defined as a clinical condition causing pain localized by the patient between the thorax and the pelvis. Additionally, patients must not have been admitted for the same condition in the previous 3 months.Age ≥18 yearsPatients with sufficient capacity to provide written informed consentExperimental group: Patients will be attended by physicians from the Emergency Department of Riotinto Hospital and by professionals with demonstrated training in clinical ultrasoundControl group: Patients will be attended by physicians from the Emergency Department of Riotinto Hospital and by professionals without demonstrated training in clinical ultrasound

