The sample will consist of patients over the age of 18 years presenting with abdominal pain in the emergency department, who will be assigned to the experimental group (POCUS is performed) or the control group (no clinical ultrasound is performed) consecutively. Patients readmitted for the same pathology will be ruled out. Patients will be invited by the investigators to participate freely, and the recruitment will end when the minimum sample size is reached in each cohort.

The inclusion and exclusion criteria are presented in Textbox 1.

Textbox 1.The inclusion and exclusion criteria.

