**Exclusion criteria**
Patients with readmission due to abdominal painPatients who leave the emergency department before completing carePatients followed in other regional health systems or private health carePregnant womenPatients with morbid obesityPatients with severe mental illnessPatients whose clinical severity prevents obtaining informed consentIntercurrent illness that makes participation impossible

The reasons for study discontinuation are as follows: (1) patient withdrawal, (2) withdrawal of informed consent, (3) death, (4) protocol violation, and (5) intercurrent illness preventing continued participation.

Informed consent will be obtained by the attending physician at the time of patient evaluation, prior to any study-related procedures.

For the sample size calculation, emergency department length of stay was used as the primary variable, as it is the only parameter that has been studied to date (19). A 25% reduction in the mean length of stay is expected in the intervention group compared with the control group. According to the multicenter trial [30], the mean length of stay for patients with nontraumatic abdominal pain in the emergency department was 5.2 (SD 3) hours. Assuming a 25% reduction (1.3 h) in the intervention group, with a 2-sided significance level of 0.05 and a power of 80%, and applying a Student *t*-test for independent samples, a minimum of 84 patients per group is required. Considering an anticipated 15% attrition rate, the total number of participants to be recruited will be 194 patients (97 per group).

There will be no randomization of the sample, as the 2 groups will receive the same care as normal for their pathology; however, in the experimental group, the intervention (clinical ultrasound) will also be carried out to test its effectiveness and assess whether it improves the quality of care. It is important to consider that clinical ultrasound is not a regulated ultrasound, but rather a response to a clinical question; therefore, it is not a complex intervention, and with the usual pressure of the service, it can be performed at any time of the year.

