### Statistical Analysis

A descriptive analysis will be carried out including proportions, measures of central tendency, and measures of dispersion, according to the nature of the variables (quantitative variables expressed as mean and SD and qualitative variables as a percentage). The analysis will include description and statistical analysis to identify any significant differences between men and women.

Comparison of the variables of interest and the stratification and potentially confounding variables at the start of the study will be carried out in both groups. The baseline values of the study variables will be tested for their homogeneity between the two groups (Student *t*-tests and chi-square tests, depending on the nature of the variables). There will also be a normality check for variables such as length of stay and those that require it.

The emergency department length of stay will be compared using a Student *t* test for independent samples, and a multiple linear regression model will be applied to adjust for potential confounding factors. The number of plain radiographs and complementary imaging studies in the Radiology Department will be analyzed using Poisson or logistic regression models, as appropriate. To account for multiple hypothesis testing, a Holm-Bonferroni correction will be applied.

The possible existence of potential confounding factors or the interaction of other variables in the relationship between the proposed intervention and the outcome variables will be assessed using logistic regression models. For continuous variables, it will be assessed by multiple linear regression.

In all cases, a statistical significance of 5% (*P*<.05) is required. The data will be processed and analyzed with SPSS (version 25.0; IBM Corp).

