### Variables

The main outcome variables aligned with the study objectives include the length of stay in the emergency department (measured in minutes), the number and type of radiological tests requested, the performance of bedside ultrasound (POCUS), diagnostic concordance, and the patient’s satisfaction with the care received. Sociodemographic variables such as age, sex, and distance from home, as well as clinical and procedural variables, will also be collected.

A complete list of all study variables, including their measurement units or response categories, is provided in Table 2, grouped into thematic blocks: sociodemographic, clinical, diagnostic, and outcome variables.

**Table 2. T2:** Study protocol variables.

Block and variable		Unit or format	Notes or response options
Sociodemographic			
	Identification code	Alphanumeric	Unique ID per patient
	Gender	Categorical	Male or female or other
	Date of birth	Date (dd/mm/yyyy)	Age will be calculated
	Distance to home	Kilometers	Estimated by postal code
Clinical			
	Health problems	Free text or ICD-10^a^	Comorbidities
	Current medications	Free text	List of active treatments
	Vital signs	Numeric (per parameter)	BP^b^ (mm Hg), HR^c^ (bpm), EVA^d^, temperature (°C), SatO_2_ (%)
	Reason for consultation	Free text	Chief complaint
Care process			
	Attending doctor	Code or initials	Family physician ID
	Date or time of arrival	Time stamp	Format: dd/mm/yyyy hh:mm
	Date or time of discharge	Time stamp	Format: dd/mm/yyyy hh:mm
	Origin	Categorical	Self-referred or primary care or ambulance or other
	POCUS^e^ performed	Binary	Yes or no
	POCUS findings	Free text	Based on clinical protocol
	Other tests requested	Categorical or multiple	Blood tests or ECG^f^ or other
	Radiology test performed	Categorical	X-ray or formal ultrasound or CT^g^ or none
	Interconsultation	Binary	Yes or no; specialty if applicable
Outcome			
	Diagnosis	Free text or ICD-10	Final ED^h^ diagnosis
	Discharge referral	Categorical	Home or hospitalization or specialist or follow-up
	Length of stay	Minutes	Calculated from entry and discharge times
	Satisfaction questionnaire	Likert scale or categorical	1‐5 scale or qualitative responses
	Diagnostic concordance	Binary	Yes or no (based on follow-up or second opinion)

a
*ICD-10: International Classification of Disease, Tenth Revision.*

b BP: blood pressure.

c HR: heart rate.

d EVA: Escala Visual Analógica (VAS: visual analog scale).

e POCUS: point-of-care ultrasound.

f ECG: electrocardiogram.

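### Groups are defined by the attending professional's ultrasound training, yet the sample size and the length-of-stay t test treat patients as independent; if outcomes correlate within physician, P values will be too small and a valid test has less power than calculated

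*Protocol article*

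**What the plan says.** **How groups are formed.** Textbox 1 (Inclusion criteria) makes the attending professional's training the difference between the groups. Experimental patients are seen by professionals with demonstrated ultrasound training, and control patients "by professionals without demonstrated training in clinical ultrasound". The text before the textbox, in Study Design and Setting, describes it differently: patients "who will be assigned to the experimental group (POCUS is performed) or the control group (no clinical ultrasound is performed) consecutively". The sample-size discussion adds: "There will be no randomization of the sample".

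**How the study is sized.** In the paragraph after the exclusion criteria, "emergency department length of stay was used as the primary variable". The inputs are a mean stay that "in the emergency department was 5.2 (SD 3) hours", a 25% reduction (1.3 h), and a Student t test for independent samples "with a 2-sided significance level of 0.05 and a power of 80" percent. This gives 84 per group, raised to 97 per group (194 in all) for 15% attrition. No number of physicians, intraclass correlation or design effect appears.

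**How it is analysed.** Statistical Analysis states: "The emergency department length of stay will be compared using a Student" t test for independent samples, with multiple linear regression to adjust for confounders. Radiology outcomes get Poisson or logistic regression. No physician term, random effect or cluster-robust variance is mentioned.

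**What is collected.** Table 2 records the attending doctor for each patient ("Code or initials", noted as the family physician's ID). No analysis described in the article uses it.

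**The concern.** If a patient's group follows from which doctor sees them, physicians are nested in group and the design resembles a small, non-randomised cluster comparison. Length of stay and the number of radiological tests depend in part on the attending doctor's own decisions, so some within-physician correlation is plausible. A t test for independent patients leaves between-physician variance out of the standard error of the group difference. A contrast between a handful of quicker and a handful of slower doctors can then look more certain than it is.

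Two things are at stake: the 5% error rate of the main length-of-stay comparison, which the planned Holm-Bonferroni step cannot repair because it takes the P values as given, and the 80% power claim, which assumes a physician ICC of exactly zero without saying so. The article does recognise operator variability, as a challenge in interpreting ultrasound findings (Discussion). It answers that with training and reference images, and the analysis makes no provision for it.

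**Working it through.** **Inputs from the article** (sample-size paragraph): difference 1.3 h, SD 3 h, two-sided alpha 0.05, power 80%, 84 evaluable and 97 recruited per group.

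**Assumed inputs:** physicians per group (k) and physician ICC for length of stay. The article gives neither. Equal patient numbers per physician are also assumed.

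**Step 1: the plan's own figure.** n = 2 × [(1.960 + 0.842) × 3 / 1.3]² = 83.6, so 84 per group. The stated number reproduces. At 84 independent patients per group, power is 80.2% by the normal approximation and 79.7% by the t distribution.

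**Step 2: formulas with clustering.**
- Patients per physician: m = n / k.
- Design effect: DE = 1 + (m − 1) × ICC.
- Effective sample size: n / DE per group.
- True two-sided error of the unadjusted test: 2 × [1 − Φ(1.96 / √DE)].
- Power of a valid test: noncentrality (1.3 / 3) × √(effective n / 2). The lower figure uses a t distribution with 2(k − 1) degrees of freedom, the higher one the normal approximation.

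Example, k = 5, ICC 0.05, n = 84: m = 16.8; DE = 1 + 15.8 × 0.05 = 1.79; effective n = 84 / 1.79 = 46.9; true error = 2 × [1 − Φ(1.465)] = 14.3%; noncentrality = 0.4333 × √23.5 = 2.10; power 45.5% (t, 8 df) to 55.5% (normal).

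**Step 3: results at 84 evaluable per group.**

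| Doctors per group | ICC | DE | Effective n | True error | Valid power |
|---|---|---|---|---|---|
| 15 | 0.01 | 1.05 | 80.3 | 5.5% | 76–78% |
| 10 | 0.02 | 1.15 | 73.2 | 6.7% | 70–75% |
| 10 | 0.05 | 1.37 | 61.3 | 9.4% | 62–67% |
| 5 | 0.05 | 1.79 | 46.9 | 14% | 46–56% |
| 4 | 0.10 | 3.00 | 28.0 | 26% | 28–37% |

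**Step 4: if all 97 per group are evaluable.** Length of stay comes from arrival and discharge times, so loss at the 1-month follow-up need not remove it.
- 15 doctors, ICC 0.01: DE = 1 + 5.47 × 0.01 = 1.05; power 81–84%.
- 10 doctors, ICC 0.02: DE = 1 + 8.7 × 0.02 = 1.17; power 75–80%.
- 5 doctors, ICC 0.05: DE = 1 + 18.4 × 0.05 = 1.92; power 48–59%.

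**Step 5: can more patients make up the loss?** With k fixed, evaluable patients per group for 80% power (normal approximation) = 84 × (1 − ICC) / (1 − 84 × ICC / k). At ICC 0.05:
- k = 15: 79.8 / 0.72 = 111.
- k = 10: 79.8 / 0.58 = 138.
- k = 6: 79.8 / 0.30 = 266.
- k = 4: the denominator is 1 − 1.05, which is negative, so no number of patients is enough.

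**The case against.** **The effect may be negligible.** With many doctors and a very small ICC, the true error is 5.5% and power close to 80%. If all 97 per group count, power exceeds 80% in that case. This stands. A reader might infer that the planned P values are certainly too small and that 80% power is certainly missed; the article does not support that, because it gives neither the ICC nor the number of physicians.

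**Allocation by physician is not settled.** The text before Textbox 1 assigns patients consecutively by whether POCUS is performed, and training is to be provided to professionals before the study. The two descriptions do conflict. But the consecutive wording gives no mechanism that separates group from physician, whereas the textbox makes physician training a criterion for each group. Nesting remains the natural reading.

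**Variance methods and covariates belong in an analysis plan.** This stands for the regressions: the article does not rule out a clustered variance there. It does not stand for the t test or the sample size, which the article fixes on an independent-patient basis.

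**Confounder adjustment could include physician.** It would not help as a fixed effect. When each physician is in one group, physician effects cannot be separated from the group effect.

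**It is an exploratory pilot.** That tempers the seriousness, but the article still claims 80% power, tests at 5% and corrects for multiplicity.

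**Conclusion.** The point holds in conditional form. Textbox 1, on its natural reading, nests physicians in group, while the fixed sample size and the fixed length-of-stay test treat patients as independent. For any positive within-physician correlation, the unadjusted test exceeds its 5% error rate, and a valid test has less power than the independent-patient calculation gives for the same number of patients.

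The size cannot be derived from the article. Over the illustrated range (4 to 15 doctors per group, ICC 0.01 to 0.10) it goes from nearly harmless to severe, and few doctors per group is the damaging end. A single emergency department serving almost 70,000 people makes few doctors conceivable, but the article does not say how many take part. The claim does not extend to saying that every planned analysis ignores clustering: only the t test and the sizing are fixed firmly enough for that.

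**What to change.** 1. Reconcile the two descriptions of how patients come to be in each group, and state the number of physicians per group.
2. Make the primary length-of-stay analysis a linear mixed model with a random intercept for the attending-doctor code and Kenward-Roger or Satterthwaite degrees of freedom. Cluster-robust standard errors with a small-sample correction are the alternative. With very few physicians both are fragile, and the report should say so.
3. Treat the radiology outcomes the same way: a physician random intercept in the Poisson or logistic model, or GEE with a small-sample correction.
4. Replace the 80% power statement by power over an ICC range, for example 0.01 to 0.10, at the actual number of physicians and at both 84 and 97 evaluable per group.

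**Cost.** The physician code is already collected, so the change is to the analysis text and needs no new data. The price is wider confidence intervals and a less favourable stated power. The change makes the inference honest; it does not recover lost power, which with few physicians may be out of reach at any number of patients. Nor does it remove confounding of POCUS with the skill or experience of the doctors who perform it, which is a separate bias to acknowledge as a limitation.

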**Exclusion criteria**
Patients with readmission due to abdominal painPatients who leave the emergency department before completing carePatients followed in other regional health systems or private health carePregnant womenPatients with morbid obesityPatients with severe mental illnessPatients whose clinical severity prevents obtaining informed consentIntercurrent illness that makes participation impossible

The reasons for study discontinuation are as follows: (1) patient withdrawal, (2) withdrawal of informed consent, (3) death, (4) protocol violation, and (5) intercurrent illness preventing continued participation.

Informed consent will be obtained by the attending physician at the time of patient evaluation, prior to any study-related procedures.

For the sample size calculation, emergency department length of stay was used as the primary variable, as it is the only parameter that has been studied to date (19). A 25% reduction in the mean length of stay is expected in the intervention group compared with the control group. According to the multicenter trial [30], the mean length of stay for patients with nontraumatic abdominal pain in the emergency department was 5.2 (SD 3) hours. Assuming a 25% reduction (1.3 h) in the intervention group, with a 2-sided significance level of 0.05 and a power of 80%, and applying a Student *t*-test for independent samples, a minimum of 84 patients per group is required. Considering an anticipated 15% attrition rate, the total number of participants to be recruited will be 194 patients (97 per group).

There will be no randomization of the sample, as the 2 groups will receive the same care as normal for their pathology; however, in the experimental group, the intervention (clinical ultrasound) will also be carried out to test its effectiveness and assess whether it improves the quality of care. It is important to consider that clinical ultrasound is not a regulated ultrasound, but rather a response to a clinical question; therefore, it is not a complex intervention, and with the usual pressure of the service, it can be performed at any time of the year.

To achieve the target sample size, recruitment will be conducted consecutively among eligible patients presenting with abdominal pain at the Emergency Department. All family physicians participating in the study have been informed and trained to identify and invite potential participants. The collaboration of the entire emergency care team will be essential to ensure continuous enrollment during the study period. Regular follow-up meetings will be held to monitor recruitment progress and address potential barriers.

Prior to this, training will be provided to professionals, and a common understanding will be reached on the possible main findings. This is intended to reduce clinical variability and improve the external validity of the study.

Given the limited sample size, short duration, and minimal risk involved in this pilot quasi-experimental study, a formal independent data monitoring committee has not been established. The principal investigator and the co-investigators will be responsible for monitoring trial conduct, data accuracy, and participant safety. As no data monitoring committee is planned, further details regarding its charter are not applicable.

No interim analyses are planned for this study due to its exploratory nature and short timeframe. Consequently, no predefined stopping rules have been established. The final decision to complete or terminate the study will rest with the principal investigator, based on recruitment feasibility, protocol adherence, or unforeseen safety concerns.

To ensure data integrity, a quality control procedure has been designed, including predefined field validation rules within the case report form. Participating clinicians were trained during project initiation to minimize data entry errors. Data entry will follow the case report form sequence, and filters will prompt the confirmation of extreme or illogical values. The principal investigator will perform monthly audits, and a second investigator will periodically review the database or a sample of its records. Questionnaire variables will be coded numerically, and preliminary analyses will be performed to detect inconsistencies or missing data. All efforts will focus on minimizing missing data and correcting errors promptly to reduce potential biases and ensure the reliability of the findings.

All individual participant data will be deidentified and securely stored in the REDCap platform hosted by semFYC. Access to the data dictionary, statistical analysis code, and related materials will be available upon reasonable request to the corresponding author, in accordance with ethical and data protection regulations. These materials will be used exclusively for academic or research purposes.

Table 1 shows the summary with the most frequent coded findings in clinical ultrasound.

**Table 1. T1:** Summary with the most frequent coded findings in clinical ultrasounds.

	Encoding	Image
Renal ultrasound		
Kidney cyst	E1	[figure not shown]
Renal pelvis dilatation	E2	[figure not shown]
Bladder polyp	E3	[figure not shown]
Kidney stones	E4	[figure not shown]
Other (specify)	E5	
Hepatobiliary ultrasound		
Cholelithiasis	H1	[figure not shown]
Biliary sludge	H2	[figure not shown]
Cholecystitis	H3	[figure not shown]
Liver angioma	H4	[figure not shown]
Metastasis	H5	[figure not shown]
Liver cyst	H6	[figure not shown]
Other (specify)	H7	
Abdominal trauma		
Abdominal free liquid	T1	[figure not shown]
Other (specify)	T2	

The study protocol is represented in Figure 1.

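### Recruiting 97 per group does not leave the required 84 per group after the stated 15% attrition; the shortfall is about 2 patients per group

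*Protocol article*

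**What the plan says.** The sample-size paragraph in Methods, Study Design and Setting (after Textbox 1) builds the trial size on one outcome: "emergency department length of stay was used as the primary variable". Its inputs come from a cited multicenter trial, "the mean length of stay for patients with nontraumatic abdominal pain in the emergency department was 5.2 (SD 3) hours", and from an expected effect, "Assuming a 25% reduction (1.3 h) in the intervention group". The error rates are given as "with a 2-sided significance level of 0.05 and a power of 80"%, with a Student t test for independent samples.

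The result is that "a minimum of 84 patients per group is required". The next sentence turns this into a recruitment target: "Considering an anticipated 15% attrition rate, the total number of participants to be recruited will be 194 patients (97 per group"). The article does not say how the attrition allowance was applied, and no other section gives a different target or attrition rate.

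Earlier in the same section, before Textbox 1, the rule for closing enrolment reads: "the recruitment will end when the minimum sample size is reached in each cohort". It does not say which number it means, or whether it counts patients recruited or patients analysed.

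**The concern.** A recruitment target with an attrition allowance should leave the required number once the anticipated loss has happened. Here the required number, the loss and the target stand in two consecutive sentences, and the target fails that test on the plan's own figures.

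The stake is that the stated power, attrition rate and target cannot all be right together. One must be restated, or a reader who checks the paragraph will find that it does not close. The loose wording of the enrolment rule adds to this: the only figure the article calls a minimum is 84, while the number to be recruited is 97, so the closing rule and the target use different terms for what should be one number.

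**Working it through.** **Inputs (all from the sample-size paragraph).** Difference 1.3 h; SD 3 h; two-sided alpha 0.05 (z = 1.95996); power 80% (z = 0.84162); attrition 15%; equal groups.

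**Step 1. Reproduce the 84.**
n per group = 2 x (1.95996 + 0.84162)^2 / (1.3/3)^2 = 83.6, rounded up to **84**. The stated figure is reproduced.

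**Step 2. Reproduce the 97.**
- Multiplying: 84 x 1.15 = 96.6, rounded up to **97**, an exact match (194 in total).
- Dividing: 84 / 0.85 = 98.8, rounded up to **99** (198 in total).

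The match with the first form suggests how 97 arose. It remains an inference, because no formula is stated. Step 3 does not depend on it.

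**Step 3. Apply the stated attrition to the stated target.**
- Per group: 97 x 0.85 = 82.45, about 82, against 84 required.
- In total: 194 x 0.85 = 164.9, against 2 x 84 = 168 required.
- Largest attrition that keeps 84: 1 - 84/97 = 13.4%.
- Check of the alternatives: 98 x 0.85 = 83.3, still short; 99 x 0.85 = 84.15, sufficient.

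**Step 4. Size of the effect on power** (difference 1.3 h, SD 3 h, two-sided 0.05):

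| Analysed per group | Normal approximation | t test |
|---|---|---|
| 82 | 79.2% | 78.8% |
| 84 | 80.2% | 79.7% |

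The loss is about 1 percentage point by either method.

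**The case against.** The strongest reply is that the gap does not matter in practice. It is 2 patients per group, and the inputs are coarser than that: the SD is given as a whole number of hours. With an SD of 2.97 h instead of 3 h, the Step 1 formula gives 2 x (1.95996 + 0.84162)^2 x (2.97/1.3)^2 = 81.9, so 82 per group would suffice. The study also describes itself as a pilot of feasibility. This stands as an argument about size. It does not make the figures agree.

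A second reply is that the outcome used for sizing may hardly be subject to attrition. Table 2 calculates length of stay from the entry and discharge times, so it is complete when the patient leaves the department; losses in the 1-month follow-up need not remove it. Patients who leave before care is completed are excluded anyway. If no value were lost, 97 per group would give 85.1% power by the t test. This largely stands too, and 82 is therefore a pessimistic count for this outcome. But withdrawal of consent or a protocol violation could still remove a patient, and it is the plan that applies 15% to this calculation.

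Two stronger readings are tempting, and the document supports neither.

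- *A reader might infer that 84 is itself wrong*, because the exact t calculation first passes 80% at 85 per group (80.2%), which would lead to 85/0.85 = 100 per group. But 84 is the usual formula result, and its t-test power of 79.7% rounds to the stated 80%. That is a choice of method, not an error.
- *A reader might infer that enrolment will stop at 84 recruited*, leaving 84 x 0.85 = 71.4, about 71 analysed and 72.7% power. That requires ignoring the explicit statement that 194 are to be recruited. The rule can equally mean 97 recruited or 84 analysable, and the latter would protect the power. The wording supports a request for clarification, not a forecast of lost power.

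**Conclusion.** The point holds as a minor arithmetic correction. At the plan's own 15% attrition, its target of 97 per group leaves about 82, not 84; the target that delivers 84 is 99 per group, 4 more patients in total. Power falls from 79.7% to 78.8% by the t test. This assumes that the 15% is a share of those recruited and that it removes length-of-stay values; if fewer values are lost, the shortfall shrinks, and at 13.4% or less it disappears.

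It does not show a materially underpowered study, and it could not plausibly change the trial's conclusion. The enrolment rule is loosely worded and should be aligned with the target; no more than that follows from it.

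**What to change.** Take one of two routes in the sample-size paragraph:

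1. Keep 194 and correct the description: 97 per group retains 84 per group with attrition of up to about 13%, or gives about 79% power if attrition reaches 15%. This costs one sentence and no patients.
2. Keep 15% and correct the target to 99 per group, 198 in total. This costs 4 more patients.

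As recruitment is described as ongoing, the first route is the simpler one, and either is adequate.

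In both cases, reword the enrolment rule before Textbox 1 so that it names the recruitment target of the sample-size paragraph in place of an unspecified minimum, and so that the end of recruitment refers to one number. This costs a few words.

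### The arms differ in treating doctors as well as in the scan, and the regression as planned would count any trained-versus-untrained doctor difference as a POCUS effect

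*Protocol article*

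**What the plan says.** Four parts of the protocol article bear on this.

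- **Who treats whom.** In Textbox 1 (inclusion criteria), experimental patients are attended by emergency physicians and professionals with demonstrated ultrasound training. Control patients are attended "by professionals without demonstrated training in clinical ultrasound".
- **Why there is no randomization.** The reason given in Study Design and Setting is that "the 2 groups will receive the same care as normal for their pathology". The paragraph presents the scan as an addition in one group, made so that its effectiveness can be tested.
- **How patients reach an arm.** The same section describes patients "who will be assigned to the experimental group (POCUS is performed) or the control group (no clinical ultrasound is performed) consecutively". This names order of arrival and says nothing of the doctor on duty.
- **What is analysed and collected.** Under Statistical Analysis, length of stay is first compared by an unadjusted t test. For the adjusted analysis, "a multiple linear regression model will be applied to adjust for potential confounding factors"; the confounders are not named. Under Variables, "A complete list of all study variables, including their measurement units or response categories, is provided in Table 2". The only physician-level entry in that table is the attending doctor, recorded as a code or initials ("Family physician ID").

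**The concern.** The reason given for not randomizing works only if the scan is the one thing that separates the groups. Textbox 1 adds a second difference, the doctors. Those who have acquired ultrasound training may also differ in seniority, test-ordering habits and speed of discharge. Length of stay and radiograph requests, both main outcomes, depend partly on those decisions.

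A shorter stay in the POCUS arm could then arise without any effect of POCUS. Equally, a real effect could be masked if the trained doctors are slower for other reasons. The hypothesis and the closing conclusion attribute the change to POCUS, so the attribution is what is at stake. This is a question of bias in the estimate and is separate from whether the standard error allows for clustering by doctor.

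**Working it through.** **1. The plan's own figure.** Inputs from the sample size paragraph: mean 5.2 h, SD 3 h, 25% reduction = 0.25 × 5.2 = 1.3 h, two-sided alpha 0.05, power 80%.

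n per group = 2 × (1.960 + 0.842)² × 3² / 1.3² = 83.6, so 84. The stated 84 is reproduced (the exact t-test solution is 84.6). The standard error of the difference at 84 per group is 3 × √(2/84) = 0.463 h. The calculation treats the whole 1.3 h as the effect of POCUS.

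**2. What the comparison estimates.** Let δ be the effect of the scan and Δ the mean difference in stay between trained and untrained doctors that would exist without any scan. If trained doctors treat one arm and untrained doctors the other, the arm difference estimates δ + Δ. Adjusting for patient and visit variables leaves Δ in place unless those variables happen to carry it.

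**3. Whether the doctor code separates δ from Δ.**

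- *Fixed effects.* Take 5 doctors per arm as an example (the number of doctors is not given). The design has an intercept, arm and 9 doctor indicators, which is 11 columns, but its rank is 10. Arm is a linear combination of the other columns, so the arm effect is not identified.
- *Random effect.* Doctor effects are assumed to have mean zero within each arm. A systematic Δ therefore stays in the arm coefficient, and only the interval widens.

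The code alone does not solve the problem. It does allow characteristics of the doctor to be attached.

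**4. Illustration of size.** The documents give no difference between doctors, so 5%, 10% and 15% of 5.2 h are assumptions. Probabilities are two-sided, from the noncentral t with 166 df, for the unadjusted t test.

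| Assumed Δ | Bias (h) | Share of 1.3 h | P(significant), no scan effect, trained doctors faster | Power for 1.3 h, trained doctors slower |
|---|---|---|---|---|
| 0% | 0 | 0% | 5% | 79.7% |
| 5% | 0.26 | 20% | 8.6% | 60.8% |
| 10% | 0.52 | 40% | 20.1% | 38.8% |
| 15% | 0.78 | 60% | 38.8% | 20.1% |

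The last column uses a net difference of 1.3 − 0.26 = 1.04, 1.3 − 0.52 = 0.78 and 1.3 − 0.78 = 0.52 h.

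**The case against.** The other side has several fair points.

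- **Exclusive treatment is not stated.** Textbox 1 mentions emergency department physicians together with trained (or untrained) professionals, which could mean shared attendance, and consecutive assignment is described elsewhere. A reader might infer that every doctor belongs to exactly one arm. That is the likelier reading, but the text does not say so, and the collinearity argument depends on it. This stands, and it is a reason to reconcile the passages.
- **Usual care from a different doctor is still usual care.** The protocol does not claim that the doctors are the same. This softens the contradiction. It does not rescue the sentence as a reason for omitting randomization, because similar usual care does not make the doctors comparable.
- **The question may be about implementation.** The objectives concern ultrasound performed by family physicians, and the study calls itself feasibility and implementation research. On that reading the trained doctor is part of the intervention. The stated aim of testing the effectiveness of the scan points the other way, so the target is ambiguous.
- **Adjustment is not impossible.** A reader might infer that the bias can never be reduced. Experience and grade can be linked later through the doctor code, and an analysis plan may name the covariates. What stands is narrower: the variable list, declared complete, does not include these items, and the article plans no such linkage.
- **The magnitude is assumed.** Nothing in the documents supports a 5–15% difference or its direction, and the figures ignore the planned regression. This stands in full.
- **It is an open, nonrandomized pilot.** True, but it is sized at 80% power for a 25% reduction and its abstract aims to demonstrate benefit, so confounding by doctor needs explicit handling.

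**Conclusion.** The concern holds in a limited form. On the natural reading of Textbox 1, arm and treating doctor are tied together, contrary to the reason given for not randomizing and not clearly in line with consecutive assignment. As written, the regression would count a systematic trained-untrained difference as an effect of POCUS, and the doctor code used alone, as a fixed or random effect, would not remove it.

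The conclusion rests on doctors being nested in arm, on Table 2 being complete as stated, and on the target being the effect of the scan. The documents do not show that such a difference exists, which way it runs, or that a positive result would be spurious. The 0.26 to 0.78 h range shows only that a modest difference would matter against a 1.3 h target. The point should be addressed before analysis; it does not invalidate the study.

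**What to change.** 1. **Reconcile the text.** Bring the consecutive-assignment sentence, the group definitions in Textbox 1 and the paragraph on not randomizing into one account of how a patient reaches an arm. State that the groups differ in treating physician.
2. **Use the doctor code.** Link years in practice and specialist or resident status to each attending-doctor code, and derive shift for each visit from the arrival time stamp already in Table 2. Include these in the length-of-stay and radiology models, and name them in advance.
3. **Narrow the conclusion.** Word it as the effect of care by POCUS-trained physicians who scan, not of the scan alone.

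The cost is two fields per doctor, one derived variable and some wording, with no extra patients or procedures. It remains feasible with recruitment under way, because the code and time stamps are already collected. Intervals will be somewhat wider, especially if there are few doctors, and some residual confounding will remain, which is why the third step is needed even if the second is done.

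A comparison of the same doctors' stays in a complaint where POCUS is not used could serve at most as an optional descriptive check. The documents identify no such complaint, it would need data on patients outside the study, and as a model covariate it could be nearly collinear with arm.
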